## Abstract

Neurofunctional models of developmental dyslexia (DD) point out disruption of the left-lateralized reading network. In individuals with DD, the left temporo-parietal (TP) regions are underactivated during reading tasks and a dysfunctional activation of the contralateral regions is reported. After a successful reading intervention, left TP lateralization was found to be increased in children with DD. Previous studies measured the effect of modulating the excitability of the left TP cortex using non-invasive brain stimulation (NIBS) in individuals with reading difficulties, showing significant reading improvements. NIBS exclusion criteria and safety guidelines may limit its application in settings without medical supervision and in younger populations. Neurofeedback (NF) training could be an alternative intervention method for modulating the inter-hemispheric balance of the temporal–parietal regions in DD. To date, the effect of NF on reading has been scarcely investigated. Few protocols increasing beta activity in underactivated areas showed improved reading outcomes. However, none of the previous studies designed the NF intervention based on a neurofunctional model of DD. We aim to propose a study protocol for testing the efficacy of a NF training specifically designed for inducing a functional hemispheric imbalance of the tempo-parietal regions in adults with DD. A randomized clinical trial aimed at comparing two experimental conditions is described: (a) Enhancing left beta/theta power ratio NF training in combination with reducing right beta/theta power ratio NF training and (b) sham NF training.

**Clinical Trial Registration:**
www.ClinicalTrials.gov, identifier [NCT04989088].

## Introduction

Developmental dyslexia (DD) is a neurodevelopmental disorder associated with a persistent impairment in the acquisition and development of reading. Diagnostic criteria include a performance in reading speed and/or accuracy that is significantly below the norm, despite average intelligence, adequate educational opportunities, and secure socioeconomic conditions (World Health Organization, 1992; American Psychiatric Association, 2013). Due to their interferences with academic achievement, DD-related difficulties are often associated with low self-efficacy (Lackaye and Margalit, 2006; Magenes et al., 2021) and can ultimately lead to emotional and behavioral problems (Capozzi et al., 2008). At a neurocognitive level, the impaired grapheme–phoneme conversion mechanism is assumed to be based on a dysfunctional letter-speech sound integration (Richlan, 2019), associated with specifically altered brain activations.

### Neurofunctional Models of Dyslexia

Over the past two decades, cross-linguistic neuroscientific research converged on a functional neuroanatomical model of DD (Richlan, 2014). In particular, altered brain activation in readers with DD was consistently identified in the left-sided reading network (Pugh et al., 2000, 2010; Démonet et al., 2004; Shaywitz and Shaywitz, 2005). In adult typical readers, the reading system includes three circuits, namely, two posterior pathways (i.e., dorsal and ventral) processing visual and orthographic information and one anterior component connected to them. The dorsal pathway, including mainly the angular and supramarginalis gyri (Price, 1998), is involved in phonology-based decoding. The ventral pathway is centered in the posterior fusiform gyrus and represents automatic access to the visual word form area (VWFA) (Cohen et al., 2002). The anterior component is located in the left inferior-frontal gyrus (Price et al., 2001) and is implicated in the output of phonological and articulatory aspects.

The standard neurofunctional model of DD posits three activation abnormalities in the reading network, and more precisely: (1) the reduced activity of a left dorsal temporo-parietal (TP) region, including the posterior aspect of the superior temporal gyrus and adjacent parietal regions, underpinning the phonological decoding difficulty; (2) the reduced activity of a left ventral occipito-temporal (OT) region, including lateral extrastriate, fusiform, and inferior temporal regions, associated with the difficulty in fast orthographic word recognition; and (3) the overactivation of the left inferior frontal gyrus (IFG), presumably reflecting a compensatory reliance on effortful articulatory processes.

A meta-analysis of neuroimaging studies conducted about DD (Richlan et al., 2009), aimed at evaluating the aforementioned standard model, confirmed the underactivation in left TP regions, specifically in the left inferior parietal lobule (IPL), superior temporal, middle temporal, inferior temporal, and fusiform regions. In contrast to the standard model, the meta-analysis pointed out the underactivation in a left IFG region associated with lexical and sub-lexical phonological representations access, together with the overactivation in the primary motor cortex and the anterior insula, serving as a compensatory reliance on articulatory-based phonological processes. The IPL abnormality was interpreted by the authors of the meta-analysis as part of a fronto-parietal attention network, interacting with reading processes *via* top-down connections.

To better explore the developmental trajectory of these abnormalities, a second meta-analysis by the same authors (Richlan et al., 2011) considered separately neuroimaging studies carried out on children and adults. Interestingly, the left TP underactivation was found only in adults but not in children, whereas the OT dysfunction was found in both populations, and more extensively in adults. Therefore, the authors suggested that an early small left OT dysfunction becomes increasingly extended during development and is later accompanied by a left TP dysfunction. These findings led the authors to posit a new neurofunctional model of DD (Richlan, 2012), including abnormalities in OT, IFG, and IPL regions. According to this model, the left IFG underactivation reflects the deficit in accessing lexical and sublexical phonological representations, whereas the left OT underactivation reflects a deficit in both words and pseudo-word processing, which becomes even more evident with increasing demands on phonological decoding.

An fMRI meta-analysis by Paulesu et al. (2014) (1) confirmed the underactivation of a left-lateralized network including the inferior frontal, premotor, supramarginal cortices, and the infero-temporal and fusiform regions and (2) excluded a specific activation of the left OT cortex in DD during reading and reading-like tasks.

Besides the left hemisphere underactivation, a dysfunctional increased right activation during reading tasks has been reported in individuals with DD (Shaywitz et al., 1998; Sarkari et al., 2002; Eden et al., 2004; Simos et al., 2007; Rimrodt et al., 2009). Although less consistent than the reduced left-sided activation, the right hemisphere overactivation was identified starting from the early phases of reading development, as in second-grade students (Bach et al., 2010), and has been interpreted as the effect of a compensatory activity during reading. Coherently, neuroimaging studies concerning intervention addressed to DD showed a reduction of right temporal activation after a successful reading intervention in children with DD (Shaywitz et al., 2004) and greater activation of the same area in children with DD who did not show reading improvements after a cognitive intervention (Odegard et al., 2008).

### Neuromodulatory Intervention for Dyslexia

The neuro-functional reorganization following an intervention addressing DD in those who exhibited a reading improvement (Eden et al., 2004; Shaywitz et al., 2004; Odegard et al., 2008; Barquero et al., 2014) inspired the possibility to use non-invasive brain stimulation (NIBS) to modulate reading performance in individuals with DD (Krause and Cohen Kadosh, 2013; Vicario and Nitsche, 2013). A systematic review by Cancer and Antonietti (2018b) discussed the findings of NIBS studies on the effect of excitability alterations in the underactivated brain regions in DD. Increased excitability of the left TP cortex using transcranial direct current stimulation (tDCS) was the most frequently investigated intervention, showing consistent positive results on reading performance in adults (Turkeltaub et al., 2012; Younger et al., 2016) and children (Costanzo et al., 2016a,b, 2019) populations. Furthermore, the neuromodulation protocols investigated by Turkeltaub et al. (2012) and Costanzo et al. (2016a,b, 2019) included the conjunction of left TP excitability and the inhibition of the right contralateral cortex. Thomson et al. (2015) attempted to measure the specific contribution of monolateral vs. bilateral stimulation in typical readers. However, findings on healthy participants showed an opposite trend as compared to the studies on individuals with DD. The authors speculated that the results of neuromodulatory intervention designed to tap into the specific brain anomalies of the brain in individuals with DD could not be replicated in healthy individuals. Further empirical evidence is needed to confirm the specific effect of the bilateral NIBS intervention.

Although its promising effect in DD, NIBS exclusion criteria and safety guidelines may limit its application in settings without medical supervision and in younger populations. The effect and safety of NIBS in children were recently reviewed by Finisguerra et al. (2019). Findings support the safety of the practice; However, long-term responses of the immature brain to stimulation should be further investigated (Cohen Kadosh, 2013; Costanzo et al., 2016a). To date, no agreement has been reached in the clinical community about the ethical aspects of using NIBS in stimulating pediatric populations (Cancer et al., 2021).

### Dyslexia and Neurofeedback

One of the most promising non-invasive methods to support individuals with DD is EEG-based neurofeedback (NF), which can encourage desirable brain activity and reduce dysfunctional brain activity through implicit mechanisms related to operant conditioning. First, EEG electrodes are placed on the scalp. The brain activity is recorded by dedicated software that analyzes it and, according to specific parameters of interest, returns feedback that can be either visual, auditory, or better, both (as a videogame). The users are familiarized with the interface and are accompanied by a professional who can provide some hints to facilitate the procedure. When the brainwaves get close to the set parameters, the users receive positive reinforcement (Au et al., 2014). This way, it is possible to create proficient and functional associations with different psychophysiological states. Such associations can more easily arise if the feedback is provided very quickly. That is why EEG has been the election choice so far. In the near majority of cases of DD-related applications, the users are children. Thus, the simpler and more fun the interface, the better. Finally, NF can also be proposed offline, for example before beginning the session to induce the ideal psychophysiological state, as well as while performing some specific exercises.

In the following paragraphs, we will briefly describe the available literature on the topic encouraging a discussion on the choices that have been made about NF training, such as the brainwaves parameters, the brain region of interest, and the type of feedback.

One of the most famous and applied NF protocols is Lubar’s one, which was tailor-made for ADHD patients. Starting from the idea that ADHD and learning disabilities present a high level of comorbidity and share some neurofunctional mechanisms, the protocol has been extended also to users with DD. The principle is to encourage β frequencies and to decrease θ ones (the so-called β/θ ratio). These kinds of training are mainly targeted at reinforcing attentional skills and visuo-motor integration (Au et al., 2014). However, with specific regard to reading abilities, it has been shown that this protocol applied with a montage over either C3 or C4 can influence visual word recognition (Barnea et al., 2005). One previous study applied this technique to explore its feasibility with the Chinese language in a pilot sample of 4 children (Au et al., 2014). The training included both unipolar protocols, intending to increase β power over C3 site, and bipolar montage involving C3 and C4, to optimize interhemispheric functional connectivity and sensorimotor integration between C3 and C4. Along with the neurophysiological recording of the different brainwave frequencies, a neuropsychological assessment was conducted before and after the NF training. The pre–post within-subject comparison revealed that the NF training increased the β/θ ratios in all participants and improved the performance in the tasks for auditory vigilance and phonological awareness.

The same protocol with β/θ ratios was adopted by Sadeghi and Nazari (2015) in a combined ERP-NF study also focused on visuo-spatial attention. The authors in this case placed the electrodes over O1 and O2 to target a most posterior network and were able to observe positive effects of the training at a behavioral level: the participants showed a reduction in the reaction times and an increase in the correct responses. Such improvement was accompanied by physiological changes, such as P3a and P3b amplitude reduction, which can be interpreted by postulating a decreased attentional demand at the neural level.

Interestingly, Nazari et al. (2012) used a similar protocol with a training set to decrease δ and θ and to increase β at T3 and F7 taking into account the double-deficit theory of DD (Arns et al., 2007). However, in this case, the authors directly explored the effects of the training over more specific linguistic skills, such as phonological awareness and reading abilities. The results of this study highlighted a significant improvement in these outcomes along with a normalization of coherence of the band power in different couples of electrodes. According to the authors, these kinds of changes could indicate integration of sensory and motor areas that could explain the behavioral advantage. This approach was also applied by Raesi et al. (2017), who found significant improvements in accuracy, comprehension, and spelling after the training.

More recently Eroğlu et al. (2020) published a research paper with two main important features. First, they used multiscale entropy analysis (MSE) for measuring dynamical complexity in the temporal features of the brainwaves. Second, they applied a protocol based on a more individualized approach. Indeed, the NF training was adjusted over the EEG activity of the participants. From here on, the NF setup was aimed at: (1) reducing theta waves at Broca area if above the threshold; (2) reducing theta waves at Wernicke area if above the threshold; (3) finding the channels with the maximum absolute power of theta waves at the left hemisphere and reduce it; and (4) finding the channels with the maximum absolute power of theta waves at the right hemisphere and reduce it. Although they did not consider behavioral outcomes, the researchers were able to observe that, after the training, the lower complexity of participants with DD increased to the typically developing group’s levels.

Finally, Breteler et al. (2012) designed a treatment that was still personalized to each individual but considering the presence of hypocoherence between couples of channels. Data analysis showed that the most common connections found to be too low were between occipital–parietal and frontal–temporal regions and parietal to medial temporal connections. In this case, the authors also considered behavioral outcomes for reading abilities. Results underlined that, after the treatment, the experimental group improved its reading scores.

To the best of our knowledge, despite the significant results obtained in previous NF research, no study has investigated a bilateral NF intervention targeting TP activation. The conjunction effect of the left increased and right decreased TP activation was found to be effective in NIBS interventions for Turkeltaub et al. (2012); Costanzo et al. (2016a, b); Younger et al. (2016).

Our hypothesis is to induce a reading performance improvement using bilateral NF to restore the typical TP hemispheric imbalance in the brain (Shaywitz et al., 1998; Sarkari et al., 2002; Eden et al., 2004; Simos et al., 2007; Rimrodt et al., 2009). As compared to NIBS, NF has fewer exclusion criteria and limitations in its application and could be safely applied in pediatric populations.

The present study protocol was designed to test the effect of a single-session bilateral NF protocol aimed at increasing the β/θ ratio in left TP areas and decreasing the β/θ ratio in the contralateral area on bilateral TP hemispheric imbalance during linguistic tasks in adults with DD. The second purpose of the study is to explore whether and to what extent the degree of asymmetry in the β/θ ratio can influence the outcomes of the training. Finally, the study aims at exploring the effect of the novel NF protocol on the reading and phonological skills of participants.

## Methods and Analyses

### Design

To test the effectiveness of a bilateral NF TP protocol for improving reading in adults with DD, a randomized controlled trial was designed. More precisely, participants will be randomly allocated to one of two parallel conditions, namely (a) the experimental condition (i.e., enhancing left β/θ and reducing right β/θ NF training); or (b) the placebo comparator (i.e., sham NF training). The trial protocol was registered on Clinicaltrials.gov (Clinical Trial ID: NCT04989088).

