## Expected Results

According to our hypothesis, the experimental single-session bilateral TP NF protocol (enhancing left β/θ and reducing right β/θ) would restore the typical reading-related inter-hemispheric imbalance in adults with DD. Accordingly, we expect to find an enhanced left β/θ power ratio and a concurrent reduced right β/θ power ratio during the performance of linguistic tasks after the active NF training. Conversely, we expect the control group (i.e., placebo NF training) to maintain an abnormal activation of TP regions during the linguistic tasks (i.e., reduced left β/θ and enhanced right β/θ) and no modulation of the β/θ power ratio after training. In summary, we expect a significant Phase (pre vs. post) × Condition (active NF vs. placebo NF) interaction effect on the modulation of bilateral TP imbalance. Also, we expect these improvements to be greater for those participants with larger asymmetry scores as assessed in the screening phase.

As for the behavioral measures (i.e., reading, RAN, and verbal WM), despite previous evidence on cognitive enhancement after a single-session NF (e.g., Escolano et al., 2014), we did not formulate a specific hypothesis, but instead, we opted for an exploratory approach, due to the potential limited effect size of a novel single-session NF protocol in DD.

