A limitation of the present study protocol is the use of a low-resolution two-channel EEG. This EEG setup was selected, instead of a higher-resolution setup, for both practical reasons (it is the equipment which is most widely used to deliver treatments), and for studying the specific locations which are the object of the present protocol, namely bilateral TP, which are particularly relevant for DD neurofunctional basis.

Despite the discussed limitations, the present study protocol would be the first attempt to adapt the neuromodulation hypothesis of DD for NF training by testing both the feasibility and efficacy of a novel rehabilitation procedure for DD, and would finally lay the groundwork for future NF applications for DD.

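### Reading is the trial's stated objective in one place and exploratory in another, and the analysis section does not separate the two roles

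*Protocol article*

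**What the plan says.** **Where reading is the objective.** The Design section opens with "To test the effectiveness of a bilateral NF TP protocol for improving reading in adults with DD, a randomized controlled trial was designed". The introduction, under Dyslexia and Neurofeedback, states: "Our hypothesis is to induce a reading performance improvement using bilateral NF to restore the typical TP hemispheric imbalance in the brain". The closing paragraph of the Discussion describes the study as "testing both the feasibility and efficacy of a novel rehabilitation procedure for DD".

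**Where reading is exploratory.** The final paragraph of the introduction lists three aims. The first is the effect of one session "on bilateral TP hemispheric imbalance during linguistic tasks in adults with DD". The second is the influence of asymmetry on the outcome. The third reads: "Finally, the study aims at exploring the effect of the novel NF protocol on the reading and phonological skills of participants". Expected Results predicts a significant Phase × Condition interaction on bilateral imbalance. Of reading, rapid automatized naming (RAN) and verbal working memory it says "we did not formulate a specific hypothesis, but instead, we opted for an exploratory approach". It explains this choice by the small benefit that one session might bring.

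**Analysis.** Data Analyses plans a 2 × 2 mixed ANOVA for each dependent measure. Its single list runs from EEG powers and ratios through linguistic-task performance to reading, RAN and digit span. A sentence on Bonferroni correction follows, without a family or a divisor. The power statement (40 participants, η² = 0.06, alpha 0.05, power 0.87) names no outcome.

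**Timing.** Under Procedure, behavioural tests are given before training and again as phase 5 of one visit of about 90 minutes. That is after NF1 and NF2 and before NF3.

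**The concern.** Reading cannot be both the hypothesis of the trial and an outcome for which no hypothesis was formed. An analysis plan cannot settle this by itself, because the objective itself is stated in two ways.

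Two things are at stake:

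- **Interpretation.** A favourable reading result could be reported as meeting the objective in the Design section. An unfavourable one could be set aside as exploratory under Expected Results.
- **The EEG test.** If every measure in the Data Analyses list counts towards the Bonferroni divisor, the exploratory behavioural scores make the threshold stricter for the hypothesis the trial was built to test. Removing them after the data are seen would be a post hoc choice.

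**Working it through.** **1. The role of reading, section by section**

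| Section | Role of reading |
|---|---|
| Introduction, hypothesis sentence | the hypothesis |
| Introduction, list of aims | last aim, exploratory |
| Design | purpose of the trial |
| Data Analyses | one of many measures, no rank |
| Expected Results | no hypothesis, exploratory |
| Discussion, close | efficacy of a rehabilitation procedure |

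The first and third rows name reading only. RAN and digit span are never put forward as an objective, so the measures whose role changes are the reading scores: 3 tasks × 2 scores (speed, errors) = 6.

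**2. The plan's own power figure**

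Inputs from Data Analyses: N = 40, η² = 0.06, alpha = 0.05, two groups, two phases. The pre-post correlation ρ is not stated; 0.5 is assumed.

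- f² = 0.06 / (1 − 0.06) = 0.0638, so f = 0.2526.
- Noncentrality for the interaction: λ = f² × N × 2 / (1 − ρ) = 0.0638 × 40 × 2 / 0.5 = 10.21, on 1 and 38 degrees of freedom.
- Power = 0.876. With f rounded to 0.25, λ = 10.0 and power = 0.869.

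The stated 0.87 is reproduced. It depends on ρ: with f = 0.2526, power is 0.60 at ρ = 0, 0.75 at 0.3 and 0.98 at 0.7.

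**3. Effect of family size on one EEG test**

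The effect and ρ = 0.5 are as above, with alpha divided by the number of tests k. The plan does not state k, so these values are illustrations.

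| k | alpha / k | power |
|---|---|---|
| 1 | 0.05 | 0.876 |
| 4 | 0.0125 | 0.714 |
| 6 | 0.0083 | 0.659 |
| 10 | 0.005 | 0.588 |
| 18 | 0.0028 | 0.507 |
| 20 | 0.0025 | 0.492 |

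Behavioral Measures gives at least 6 reading scores + 2 RAN scores (speed, errors) + 2 digit spans = 10. Suppose the confirmatory family were the left and right β/θ ratios in each of the two linguistic tasks, so 2 × 2 = 4 tests. Adding the ten behavioural scores gives 14. Power then falls from 0.71 to a value between the rows for 10 and 18, that is between 0.59 and 0.51.

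**4. What the sample size means for reading**

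The same λ expressed as a between-group difference d in pre-post change: λ = (N / 4) × d², so d = √(4 × 10.21 / 40) = 1.01 SD. That is large beside the limited effect that Expected Results foresees for a single session, so the 0.87 gives no assurance for reading.

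**5. Timing of the reading post-test**

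Training before the post-test is 10 + 20 = 30 minutes of the planned 10 + 20 + 10 = 40. Neurofeedback Protocol says NF3 is meant to make changes last through both the behavioural post-assessment and the EEG recording. In Procedure, the behavioural post-assessment precedes NF3. The two sections conflict.

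**The case against.** The strongest reply is that the status of reading is already fixed in advance. The list of aims and Expected Results both call it exploratory, the latter with a reason, and the Discussion says the interest is mainly neurophysiological. On this view the fault is loose wording in a few sentences. Much of this stands: the explicit statements favour the exploratory reading. It does not remove the contradiction with the Design section, and it does not supply the distinction missing from the Data Analyses list.

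The Discussion also justifies the single session openly, as a first test that could inform longer programmes. That stands too. The lack of a later visit is a limit on what may be claimed, not an error.

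A reader might infer more than the document supports:

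- **That the trial cannot answer its objective.** The design can address the imbalance aim, and a randomised sham comparison with reading measured before and after training can estimate an immediate effect on reading.
- **That reading is tested only once.** There is one post-training test, but also a pre-training test.
- **That six reading tests at 0.05 carry a 26% chance of a false positive** (1 − 0.95⁶ = 0.265). This assumes uncorrected, independent tests. Bonferroni is planned, and speed and error scores on related tasks in the same people are unlikely to be independent.
- **That no conclusion on reading is permissible.** Labelling it immediate and exploratory is enough.

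**Conclusion.** The contradiction is real and should be fixed, but it does not invalidate the design. The Design section and the hypothesis sentence of the introduction make reading the objective; the list of aims and Expected Results make imbalance during the linguistic tasks the only hypothesis. Data Analyses does not carry that distinction.

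The consequences are an ambiguous claim for the six reading scores and a possible loss of power for the EEG hypothesis, from 0.876 uncorrected to 0.59 with ten tests in the family. These power figures rest on ρ = 0.5, on the plan's η² of 0.06 and on assumed family sizes. The stated power of 0.87 is itself reproduced under that ρ. Any reading result can be read as an immediate effect within the visit, measured before training is complete; it cannot be read as confirmed or lasting efficacy.

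**What to change.** - In the introduction, the Design section and the close of the Discussion, bring the wording into line with Expected Results. Name the effect of active versus sham training on temporo-parietal β/θ imbalance during the linguistic tasks as the confirmatory objective.
- In Data Analyses, define the confirmatory Bonferroni family and keep reading, RAN and digit span outside it. Report them as exploratory estimates with confidence intervals.
- Describe any reading result as an immediate, exploratory effect, not as efficacy of a rehabilitation procedure.
- Reconcile Procedure with Neurofeedback Protocol on the order of the behavioural post-test and NF3.

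The first and third changes are wording only. The second changes the analysis: the divisor for the EEG tests shrinks, and the behavioural tests lose confirmatory error control. The price is a narrower claim. None of these first three changes alters the sample size or the assessments; what the last one requires depends on how the sponsor reconciles the two sections.
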